### 2.10 Blinding

This study is designed to be a double-blind trial. During the experiment, neither participants nor researchers had group information. The medication number, label, and packaging for each participant were prepared from 001 to 030. Random numbers were sealed in double opaque envelopes, which were kept by [name], who was responsible for the blind method management. Every participant received their corresponding emergency letters, which were kept until the end of the trial.

### 2.11 Outcome measures

Assessments were performed at the baseline (T0), 4 weeks after the final treatment (T1, primary endpoint), 8 weeks after the final treatment (T2, secondary endpoint, first follow-up 8 weeks after the final treatment), 12 weeks after the final treatment (T3, tertiary endpoint, second follow-up 12 weeks after the final treatment), and 16 weeks after the final treatment (T4, final endpoint, third follow-up 16 weeks after the final treatment). The timeframe of data collection and assessments is shown in Figure 3 (the SPIRIT figure).

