## Abstract

**Introduction:** Anal fistula is one of the commonest ailments seen by anorectal surgeons as surgery is currently the preferred treatment for it. Diabetes mellitus is a risk factor that can lead to slow wound healing after anal fistula surgery. Because of the large postoperative wound surface of anal fistula, patients with diabetes can have an increased probability of wound infection, which makes it hard to heal. There is an extensive clinical experience for wound healing in traditional Chinese medicine (TCM). The Jiedu Shengji decoction (JSD) is a widely used external washing decoction in clinical practice. However, the current evidence on it is still insufficient. Therefore, we report this carefully designed clinical trial to assess the efficacy and safety of JSD in the treatment of postoperative wounds in diabetic patients with anal fistula.

**Methods and analysis:** This study was designed to be a randomized, double-blind, placebo-controlled, multi-center clinical trial. There were 60 eligible participants who were randomized at a 1:1 ratio to the intervention and placebo groups. Both groups received the same standard treatment. The intervention group was given external washing decoction of TCM (JSD), while the placebo group was given the placebo made of excipients and flavoring agents. The main outcome measures include wound healing, distribution of wound pathogens, levels of inflammatory mediators, and blood glucose. The secondary outcome measures included lipids, the quality of the life evaluation scale (Short-Form Health Survey 36). Assessments were performed before the start of the study, at 1st, 2nd, 3rd, and 4th weeks after the intervention, and at 8th, 12th, and 16th follow-up weeks.

**Discussion:** The clinical study we proposed will be the first randomized, double-blind, placebo-controlled, multi-center clinical trial study to assess the efficacy and safety of TCM external washing (JSD) in the treatment of postoperative wounds in diabetic patients with anal fistula.

**Ethics and dissemination:** The Medical Ethics Committee of Hospital of Chengdu University of Traditional Chinese Medicine has reviewed this study protocol and gave its approval and consent on 17 March, 2022 (Ethical Review Number: 2022KL-018).

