Bai Zhi [*Angelica dahurica* (Hoffm.) Benth. Et] Hook. f. ex Franch. et Sav]	Roots	Sichuan Chinese Herb Preparation Co., Ltd., Sichuan, China	20	Washing and sitz bath for 30 min	Liquid, 200ml, once a day, last 4 weeks	Y-registered in relevant administration	Y-prepared according to the manufacturer	The drugs are sealed and stored in a Chinese medicine warehouse at 0–30°C and 45–75% humidity
Ercha [*Acacia catechu* (L. F.) Willd]	Dry extract of skin, branch, and stem	Sichuan Chinese Herb Preparation Co., Ltd., Sichuan, China	20	Washing and sitz bath for 30 min	Liquid, 200ml, once a day, last 4 weeks	Y-registered in relevant administration	Y-prepared according to the manufacturer	The drugs are sealed and stored in a Chinese medicine warehouse at 0–30°C and 45–75% humidity

The placebo group was given placebos made of excipients and flavoring agents. Placebo formula: pyrosyrup (edible), apple green (edible), and lactose (medicinal). Placebos were packaged, shaped, and colored to be the same as JSD. Placebos were produced by the Placebo Experimental Center of School of Pharmacy, Chengdu University of Traditional Chinese Medicine, which had no efficacy or side effects. The external washing decoction was placed in a special vessel and air-dried to lukewarm for patients to take sitz bath for 30 min/time. Then, the bases of incisions were packed outward along with a gauze in moderate tightness. The incisions were covered with sterile gauze and fixed with adhesive plaster. The wound dressing was changed once a day for 4 weeks. We followed up the participants at the 8th, 12^th^, and 16th weeks after the dressing change was finished to record and analyze the recurrence.

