### 2.12 Primary outcomes

#### 2.12.1 Wound healing

Assessments were at T0, T1, T2, T3, and T4. At the same time, weekly assessments were conducted during weeks 1–4 of intervention.1) Wound healing rate: The wound area on the first postoperative day was the original area. The maximum length and width of the wound were measured with the calculated area. Formula: Wound healing rate = (original area-current area)/original area × 100%.2) Wound healing time: From the start of the dressing change to the complete epithelialization and healing of the wound.3) Wound secretion score (Table 2) (Gould et al., 2021): Wound with abundant secretion, two or more pieces of penetrated gauze, dressing change more than twice a day, 3 points; wound with much secretion, one piece of penetrated gauze, dressing change twice a day, 2 points; wound with little secretion, no penetrated gauze, 1 point; and wound with smooth surface and no obvious secretion, 0 point.4) Wound edema score (Table 2) (Gould et al., 2021): Wound with severe edema which is significantly more than the wound edge, surgical resection needed, 3 points; wound with obvious edema which is more than the wound edge, need dressing change to remit, 2 points; wound with mild edema, 1 point; and wound with no edema, 0 point.5) Granulation tissue color score (Table 2) (Gould et al., 2021): Bright red, 1 point; light red, 2 points; and purple, 3 points.6) Anal function evaluation: The Wexner incontinence score was used to evaluate the anal function of participants after wound healing (Zhang et al., 2020a), including the ability of the anus to control the intestinal fluid, bowel gas, and loose and formed stools.7) Anal pain score: The pain index tested before the dressing change on the first postoperative day was the baseline pain. The pain index after the first postoperative day was tested within 2 h after the dressing change. Pain values were tested using the visual analogue scale (Anal pain visual analogue scale, VAS) (Bondi et al., 2017).

**TABLE 2 T2:** Scale for assessing wound healing.

Wound secretion score (Gould et al., 2021)	Score
Would with smooth surface and no obvious secretion	0
Would with little secretion and no penetrated gauze	1
Wound with much secretion, one piece of penetrated gauze, and dressing change twice a day	2
Wound with abundant secretion, two or more pieces of penetrated gauze, and dressing change more than twice a day	3
Wound edema score (Gould et al., 2021)	Score
Wound with no edema	0

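### The date of T1, the declared primary endpoint, is internally inconsistent: Section 2.11 puts it at week 8 from the start of treatment, while other parts of the article point to the end of week 4

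*Protocol article*

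**What the plan says.** Section 2.11 is the only place that dates T1. It gives "4 weeks after the final treatment (T1, primary endpoint", and then describes the next visit as "T2, secondary endpoint, first follow-up 8 weeks after the final treatment". T3 and T4 follow at 12 and 16 weeks after treatment and are numbered second and third follow-up.

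Section 2.8 fixes the length of the course: "The wound dressing was changed once a day for 4 weeks". It then names visits at 8, 12 and "16th weeks after the dressing change was finished to record and analyze the recurrence".

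The abstract lists assessments before the start, then "at 1st, 2nd, 3rd, and 4th weeks after the intervention, and at 8th, 12th, and 16th follow-up weeks".

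Section 2.12.1 (wound healing) lists T0 to T4 and adds that "weekly assessments were conducted during weeks 1–4 of intervention"; Section 2.13 (secondary outcomes) does the same. Sections 2.12.2 (pathogens) and 2.12.3 (inflammatory mediators) give only weekly assessments in weeks 1 to 4 of the intervention and do not mention T1. Section 2.14 schedules the safety measurements at T0 and T1 only.

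**The concern.** T1 is the visit that the plan declares to be its primary endpoint, so its date decides what the trial estimates. At week 4 the comparison is made at the end of exposure. At week 8 it is made after four weeks without the study wash, on a wound that has gone on closing. These are different treatment effects.

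Three consequences would follow from the literal date:

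- Two of the four primary outcome groups would have no stated measurement at the primary endpoint.
- Wound healing would be recorded at both week 4 and week 8. If T1 is not settled in advance, either value could be presented as the primary comparison after the data are known.
- The only scheduled post-baseline vital signs, laboratory tests and electrocardiogram would be taken four weeks after exposure ended.

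**Working it through.** The check puts every schedule on one scale, weeks from the start of treatment. The course lasts 4 weeks (Section 2.8; also Table 1), so k weeks after the final treatment is week 4 + k.

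| Source | What is listed | Weeks from start |
|---|---|---|
| 2.11, literal | T1 to T4 at 4, 8, 12, 16 weeks after treatment | 4+4 = 8, 4+8 = 12, 4+12 = 16, 4+16 = 20 |
| 2.8 | 8, 12, 16 weeks after the last dressing change, for recurrence | 12, 16, 20 |
| Abstract, weeks 1–4 on treatment, follow-up counted from the end | four weekly visits, three follow-ups | 1–4, 12, 16, 20 |
| Abstract, everything counted from the start | the same | 1–4, 8, 12, 16 |
| Abstract, everything counted from the end | the same | 5–8, 12, 16, 20 |
| 2.12.1 and 2.13 | T0 to T4, plus weekly visits on treatment | 1–4, plus T1 to T4 |
| 2.12.2 and 2.12.3 | weekly visits on treatment only | 1–4 |
| 2.14 | T0 and T1 | 0 and T1 |

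**T1 at week 8 (Section 2.11 as written).** This agrees with Sections 2.12.1 and 2.13, where T1 and the fourth weekly visit are then two distinct visits. It sits badly with the numbering in Section 2.11 itself, because the visit at week 12 is called the first follow-up although week 8 is already off treatment. It is absent from Section 2.8 and from the first reading of the abstract. Sections 2.12.2 and 2.12.3 then state nothing at T1.

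**T1 at week 4 (end of course).** This agrees with the follow-up numbering, with Section 2.8, with the first reading of the abstract, and with Sections 2.12.2 and 2.12.3. It contradicts the only explicit date, and it makes T1 and the fourth weekly visit in Sections 2.12.1 and 2.13 the same visit listed twice.

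**Can another reading of the abstract rescue the text?** Counted from the start, its week 8 matches a literal T1, but week 20 (T4) has no visit and Section 2.8 is contradicted. Counted entirely from the end, its fourth weekly visit also lands on week 8, but then the weekly visits come after treatment, against Sections 2.12.1, 2.12.2, 2.12.3 and 2.13, which place them during it.

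**Gap between the candidate dates:** 8 − 4 = 4 weeks, as long as the treatment course itself.

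The sample size section does not settle the matter. Its planning healing rates (33.35% and 27.33%) carry no time point.

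**The case against.** The strongest defence is that T1 has one stated date, and that date is explicit. No sentence says that T1 is the end of the course; that date is reached only by elimination. This is correct. A reader might infer that the article states two rival dates for T1, and it does not.

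Three further points weaken the elimination:

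- The visits in Section 2.8 are given a purpose, recurrence, so the list need not be complete. The follow-up numbering in Section 2.11 could be the numbering of those recurrence visits.
- Sections 2.12.1 and 2.13 list T1 beside the weekly visits, which favours the literal date.
- The abstract is condensed and its wording is loose.

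Figure 3, to which Section 2.11 refers for the timing, is not visible here and may show what was meant. The sites presumably also hold a fuller protocol, so it cannot be assumed that the three hospitals measure at different times.

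A reader might also go on to claim a loss of power from mixing week-4 and week-8 readings. The documents do not support that. Section 2.12.1 schedules a week-4 wound assessment for everyone on either reading, so a mixture would arise only if an analyst pooled different visits as one variable. Any figure would also need an assumed healing curve, an assumed week for the planning means and assumed shares of participants.

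What the defence does not remove is the conflict in the text. The literal date leaves the numbering in Section 2.11 awkward, lacks clear support in the abstract, and leaves two primary outcomes without a stated measurement at the primary endpoint.

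**Conclusion.** The concern holds as an inconsistency in the date of the declared primary endpoint. The literal date is week 8; the date implied by elimination is week 4; no reading fits all the sections. The size is four weeks in the timing of the primary comparison, and it reaches two of the four primary outcome groups and the only scheduled post-baseline safety measurements.

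This rests on the four-week course in Section 2.8 and on the text alone, without Figure 3. Even a clear figure would leave the abstract, Section 2.11 and the outcome sections to be reconciled. It is not concluded which date was intended, that sites have measured at different times, or that power is reduced.

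**What to change.** Before any unblinded look at the data:

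1. State T1 as one date, in weeks from the start of treatment, and express T2 to T4 on the same scale.
2. Use it consistently in the abstract and in Sections 2.8, 2.11, 2.12, 2.13 and 2.14, and check Figure 3 against it.
3. Name that visit as the single time point of the primary comparison.
4. Make the assessment times of every primary outcome agree with it, including pathogens and inflammatory mediators.
5. If the week-8 visit is meant, add it to the abstract and to the follow-up numbering. If the end of week 4 is meant, correct the date in Section 2.11 and say that T1 and the fourth weekly visit are the same.

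The cost is a wording amendment, approved as Section 3.2 requires, and a notice to the three hospitals. No extra visit is needed if T1 is the end of week 4. If it is week 8, the further cost depends on whether that visit is already being made and whether pathogen and mediator samples are to be taken at it.

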**FIGURE 3 F3:**
[figure not shown]
SPIRIT figure showing the time points for enrollment, interventions, and assessment.

### 2.12 Primary outcomes

#### 2.12.1 Wound healing

Assessments were at T0, T1, T2, T3, and T4. At the same time, weekly assessments were conducted during weeks 1–4 of intervention.1) Wound healing rate: The wound area on the first postoperative day was the original area. The maximum length and width of the wound were measured with the calculated area. Formula: Wound healing rate = (original area-current area)/original area × 100%.2) Wound healing time: From the start of the dressing change to the complete epithelialization and healing of the wound.3) Wound secretion score (Table 2) (Gould et al., 2021): Wound with abundant secretion, two or more pieces of penetrated gauze, dressing change more than twice a day, 3 points; wound with much secretion, one piece of penetrated gauze, dressing change twice a day, 2 points; wound with little secretion, no penetrated gauze, 1 point; and wound with smooth surface and no obvious secretion, 0 point.4) Wound edema score (Table 2) (Gould et al., 2021): Wound with severe edema which is significantly more than the wound edge, surgical resection needed, 3 points; wound with obvious edema which is more than the wound edge, need dressing change to remit, 2 points; wound with mild edema, 1 point; and wound with no edema, 0 point.5) Granulation tissue color score (Table 2) (Gould et al., 2021): Bright red, 1 point; light red, 2 points; and purple, 3 points.6) Anal function evaluation: The Wexner incontinence score was used to evaluate the anal function of participants after wound healing (Zhang et al., 2020a), including the ability of the anus to control the intestinal fluid, bowel gas, and loose and formed stools.7) Anal pain score: The pain index tested before the dressing change on the first postoperative day was the baseline pain. The pain index after the first postoperative day was tested within 2 h after the dressing change. Pain values were tested using the visual analogue scale (Anal pain visual analogue scale, VAS) (Bondi et al., 2017).

**TABLE 2 T2:** Scale for assessing wound healing.

Wound secretion score (Gould et al., 2021)	Score
Would with smooth surface and no obvious secretion	0
Would with little secretion and no penetrated gauze	1
Wound with much secretion, one piece of penetrated gauze, and dressing change twice a day	2
Wound with abundant secretion, two or more pieces of penetrated gauze, and dressing change more than twice a day	3
Wound edema score (Gould et al., 2021)	Score
Wound with no edema	0
Wound with mild edema	1
Wound with obvious edema, which is more than the wound edge and need a dressing change to remit	2
Wound with severe edema, which is significantly more than the wound edge, and surgical resection is needed	3
Granulation tissue color score (Gould et al., 2021)	Score
Bright red	1
Light red	2
Purple	3

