### 2.16 Sample size

According to the sample size estimation method for the comparison of two sample means, we preset the sample size of the placebo group and the intervention group for them to be equal. The calculation formula is as follows:
$$n=2\sigma^{2}\times \frac{f\left(\alpha ,\beta \right)}{{\left(\mu_{1}-\mu_{2}\right)}^{2}},$$

where *n* represents the overall sample size of the study, μ1 and μ2 are the mean values of the control group and the test group, respectively, and σ is the standard deviation. We set that the probability of making type I error in this study shall not be greater than 5%, and the probability of making type II error at the same time shall not be greater than 10%, that is, α = 0.05 and β = 0.1. Referring to Chinese literature reports on TCM external washing for the treatment of postoperative wound of anal fistula, the wound healing rate (%) in literatures was set as the clinical efficacy observation, the mean value was 33.35, and the standard deviation was 2.29 in the intervention group, and the mean value was 27.33 and the standard deviation was 2.67 in the placebo group. The estimated loss of the follow-up rate was 20%, so the total study sample size was 60, of which 30 was for the intervention group and 30 was for the placebo group.

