### 2.20 Data analysis

All data analyses were conducted by SPSS 24.0 software. Student’s t-test was performed on continuous normally distributed variables, the Wilcoxon rank-sum test on non-normal variables, and Pearson’s χ^2^ test on categorical variables. Data were presented as the mean ± standard deviation for continuous variables or percentage values for categorical variables. The statistical significance level was set at *p* < 0.05, and all the statistical tests were two-sided.

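### Wound healing time is a primary outcome that can be censored, but the analysis section names only tests that need a scoring rule for unhealed or lost wounds, and no such rule is given

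*Protocol article*

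**What the plan says.** Wound healing time is item 2 under the primary outcome of wound healing (section 2.12.1): "From the start of the dressing change to the complete epithelialization and healing of the wound". The same section schedules wound assessment weekly in weeks 1–4 and at T0 to T4. Section 2.11 places T4 at 16 weeks after the final treatment.

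The analysis section (2.20) opens with "All data analyses were conducted by SPSS 24.0 software" and then names the tests: Student's "t-test was performed on continuous normally distributed variables, the Wilcoxon rank-sum test on non-normal variables", and Pearson's chi-square for categorical variables. It names no survival method. A healing time can only fall under the t-test or the rank-sum branch.

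Three places bear on wounds that are never seen to close:
- **Section 2.16:** "The estimated loss of the follow-up rate was 20" per cent.
- **Section 2.7:** participants who stop study medication, or take other medication that could affect results, leave the study. At low withdrawal, incomplete data are cleaned. Above 10% withdrawal, imputation, intention-to-treat and sensitivity analyses apply.
- **Section 2.18:** the handling of missing data follows the data managers' view of the mechanism, with a sensitivity analysis.

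None of these gives a censoring rule or a value for an unhealed wound.

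**The concern.** A participant who leaves before closure, or whose wound is still open at the last assessment, has a healing time known only to exceed the last observation. A t-test or rank-sum test needs a number or a rank for that person. Without a stated rule, the analyst must leave the person out, enter the last visit as if the wound had closed then, impute by a method chosen later, or assign a worst rank.

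These choices do not give the same answer. Leaving out unhealed wounds removes the slowest healers. If the wash works, more of them are in the placebo arm, so the benefit is understated. Counting the last visit as healing makes the arm with more loss look faster. Sections 2.7 and 2.15 give reasons why loss might differ by arm: the wash is stopped after any adverse event, and stopping study medication ends participation.

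What is at stake is whether the comparison of one listed primary outcome is decided by a scoring choice made once the data are in hand.

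**Working it through.** **What the plan lets one reproduce.** It gives no figure for healing time. Its only calculation, section 2.16, concerns wound healing rate (means 33.35 and 27.33, SDs 2.29 and 2.67, "α = 0.05 and β = 0.1"). With pooled SD √[(2.29² + 2.67²)/2] = 2.487 and two-sided alpha, n per arm = 2 × 2.487² × (1.960 + 1.282)² / 6.02² = 3.59. That is 4 per arm, 5 after 20% loss, and 10 in total, not 60. This is a separate matter and does not bear on the present point.

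**Inputs from the documents.** 30 per arm; 20% loss; two-sided 0.05; last wound assessment at 4 weeks of treatment + 16 weeks = 20 weeks, about day 140.

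**Assumptions, not in the documents.** Lognormal healing times with medians 27 days (intervention) and 35 days (placebo), log-SD 0.4; loss at a uniformly random time. The true mean difference is (35 − 27) × exp(0.4²/2) = 8 × 1.083 = 8.7 days.

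**Share healed before any loss**, Φ[ln(C/median)/0.4]:
- C = 28: placebo Φ(−0.56) = 29%, intervention Φ(0.09) = 54%.
- C = 140: placebo Φ(3.47) = 99.97%. With 20% random loss, about 95% in each arm are seen to heal.

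**Healed-only t-test against log-rank on everyone**, 20% loss in each arm. Ranges are across repeated simulations of 1,200 trials.

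| Closure observed to | True difference | Healed-only difference | Power, t-test | Power, log-rank |
|---|---|---|---|---|
| Day 28 | 8.7 d | 1.5–1.7 d | 9–11% | 48–51% |
| Day 56 | 8.7 d | 5.7 d | 48% | 59–61% |
| Day 140 | 8.7 d | 8.6 d | 63–65% | 62% |

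**No true effect, loss 10% vs 30%, last visit counted as healing** (median 31 days in both arms):
- Day 28: type I error about 20–26% across the t-test and rank-sum test, against about 5% for log-rank.
- Day 56: about 9–10%, against about 5%.
- Day 140: about 5%.

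**A second distribution as a check.** Weibull, shape 3, medians 35 vs 28 days, true difference about 7 days:
- Day 28, no loss: 30% vs 50% heal. The healed-only difference is 0.5 day, and it is 1.8 days with censored times counted as healing. Power is 5% (t-test, healed only), 27% (t-test, censored as healed), 37% (rank-sum, censored as healed) and 38% (log-rank).
- Day 140, 20% loss: differences of 7.0 and 6.8 days. Power is 60%, 58% and 53% for those three tests, against 70% for log-rank.
- No effect (medians 30 days), loss 30% vs 10%, day 28, censored as healed: type I error 20% (t-test) and 17% (rank-sum), against 4.5% for log-rank.

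The two models agree on bias and type I error. They differ on whether log-rank gains power at day 140: nothing under the lognormal, about 10 points under the Weibull.

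**The case against.** A reader might infer that the plan as written biases the arm difference. The documents do not support that. Sections 2.11 and 2.12.1 schedule wound assessment to about day 140, and nothing says that closure is scored only to day 28 or 56. On the scheduled window, with the assumed medians, the healed-only estimate is nearly unbiased, the t-test loses no power under the lognormal model, and even 10% vs 30% loss leaves type I error near 5%. The assumed medians and spread come from outside the documents. This stands, and it limits the point.

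The rank-sum test is also not wrong in itself. If unhealed wounds share a worst rank and lost participants are excluded unless already healed, its power is 48%, 62% and 66% at days 28, 56 and 140, against 49%, 62% and 62% for log-rank, with type I error of 4–5% under equal random loss. What is lacking is the rule. One could say that such rules belong in an analysis plan that is not shown. But section 2.20 fixes the tests for all analyses, and the stated choice does not fit a time that may be censored.

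Section 2.7 does promise imputation and intention-to-treat analysis above 10% withdrawal, which the expected 20% would trigger. That is a fair reply to any claim that participants will certainly be dropped. It still gives no rule for a right-censored time.

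A reader might also infer that closures after week 4 are known only to within 4 weeks. Dressing is changed daily for 4 weeks, so closures in that period can be dated to the day. No section says that later closures are dated only at visits. The calculations above do not model this.

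Finally, log-rank and Cox assume non-informative censoring. They do not cure removal under section 2.7 if it is related to healing.

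**Conclusion.** The point holds as a mismatch between outcome and method. Healing time can be censored on the plan's own terms, and section 2.20 names only tests that cannot handle a censored time without a scoring rule that the plan does not give.

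The documents do not fix the size of the resulting error. On the assumed distributions it runs from negligible (closure observed to about day 140, equal random loss) to severe (scoring stops at day 28: about 1.5 days shown for a true 8.7). False positives appear when last visits count as healing, loss differs by arm and the scoring window is short. More distortion than the day-140 figures show would arise if many wounds stayed open at the last visit.

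Healing time is one of several measures under the primary heading, and the sample size was set on healing rate. This is something the sponsor should correct, not a flaw that invalidates the trial.

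**What to change.** In section 2.20, state that wound healing time is analysed for all randomised participants by Kaplan-Meier curves and a log-rank test, with a Cox hazard ratio (adjustment for original wound area is optional). Censor participants whose wound has not been seen to close at their last wound assessment.

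Add two sensitivity analyses:
- One for informative removal under section 2.7, for example treating removed participants as unhealed to the last scheduled visit.
- An interval-censored analysis, if closures after week 4 are dated only at follow-up visits. If they are dated between visits, say so and leave this out.

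The cost is a few sentences and a little analysis work, with no new data. The named software covers the main analysis. The change does not make the trial powered for healing time. With 48 healing events (60 less 20%), log-rank power by Schoenfeld's formula is 29%, 67%, 89% and 97% at assumed hazard ratios of 1.5, 2.0, 2.5 and 3.0.

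### The granulation colour score has no value for a closed wound, so at T1–T4 it can compare the arms only among wounds still open unless closed wounds are given a value

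*Protocol article*

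**What the plan says.** Section 2.12.1 lists seven wound-healing items under the primary outcomes. Item 5, granulation tissue colour, is scored "Bright red, 1 point; light red, 2 points; and purple, 3 points", and Table 2 repeats the same three levels. The two neighbouring scales start at 0. For secretion, the lowest level is "wound with smooth surface and no obvious secretion, 0 point", and for edema it is the absence of edema. A healed wound can take either of these values.

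The section opens with one schedule for its items: "Assessments were at T0, T1, T2, T3, and T4. At the same time, weekly assessments were conducted during weeks 1–4 of intervention". Section 2.11 places the first post-treatment visit at "4 weeks after the final treatment (T1, primary endpoint") and the last, T4, at 16 weeks after the final treatment. Closure is an expected event, since healing time runs "From the start of the dressing change to the complete epithelialization and healing of the wound" and the Wexner score is taken after healing.

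No section says what colour value a closed wound receives. The missing-data rule in section 2.7 is triggered by withdrawal, not by healing. Section 2.18 leaves the method to the data managers' view of the missingness mechanism, with a sensitivity analysis. Section 2.20 specifies two-group tests.

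**The concern.** Every level of the colour score, including the best, describes granulation tissue that is still visible. Once a wound has epithelialised, the participant has done as well as the trial hopes and yet has no admissible score. If that cell is left blank, the late colour comparison is restricted to wounds that have not healed. That group is defined by a post-randomisation outcome that treatment is meant to influence, and it shrinks faster in the arm that heals better. Randomisation no longer protects the contrast.

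The score belongs to the primary-outcome group and T1 carries the primary-endpoint label, so the late comparison could be read as confirmatory evidence on wound quality.

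**Working it through.** **Scale against schedule.** Secretion runs 0–3 and edema 0–3, and both have a usable value after closure. Colour runs 1–3 and has none. Treatment lasts 4 weeks (section 2.8). Read with section 2.11, T1 therefore falls about 4 + 4 = 8 weeks, and T4 about 4 + 16 = 20 weeks, after dressing changes begin. T0 is unaffected, as are weekly visits while all wounds are open.

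**Inputs for an illustration.** From the document: 30 per arm and 20% expected loss (section 2.16), so 30 × 0.8 = 24 evaluable per arm; two-sided tests at 0.05 (section 2.20). Assumed, because the document gives no such figures: 40% closed on placebo and 60% on JSD; one latent normal wound state driving both closure and colour; placebo open wounds split equally over the three colours.

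**Numbers scored.** Open wounds: 24 × 0.60 = 14.4 on placebo and 24 × 0.40 = 9.6 on JSD.

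**Mean scores.** The latent shift that moves closure from 40% to 60% is 0.2533 + 0.2533 = 0.507 SD. On placebo the proportions are closed 0.40 and colours 1, 2, 3 at 0.20 each, so the open-wound mean is 2.00. On JSD the shifted distribution gives closed 0.600, colour 1 0.176, colour 2 0.135 and colour 3 0.089, so the open-wound mean is (0.176 + 2 × 0.135 + 3 × 0.089) / 0.400 = 1.78.

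| Handling of closed wounds | Placebo | JSD | Difference | Rank-sum power, 24 evaluable per arm |
|---|---|---|---|---|
| Not scored | 2.00 | 1.78 | -0.22 | about 7–10% |
| Coded 1 | 0.40 + 1.20 = 1.60 | 0.60 + 0.71 = 1.31 | -0.29 | about 26–27% |
| Coded 0 | 1.20 | 0.71 | -0.49 | about 31–33% |

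Power was simulated; the ranges cover repeated runs.

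**How much of this is colour?** Suppose JSD has no effect on colour, colour is unrelated to closure, and the mean colour is 2 in both arms. Coding closed as 0 then gives 2 × 0.40 - 2 × 0.60 = -0.40 from closure alone. Coding it 1 gives (0.60 + 0.80) - (0.40 + 1.20) = -0.20. Neither figure in the table is a pure colour effect that the open-only analysis simply underestimates.

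**Direction of the open-only bias.** It depends on the link between colour and closure:
- One shared state: the difference is attenuated, as in the table.
- Colour independent of closure: there is no bias, only fewer wounds. A colour effect of -0.36 is recovered as -0.36.
- Correlation 0.5 and no effect of JSD on colour: the open-only difference is about +0.13, against JSD.

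**Sensitivity to the closure share.** If only 2% of placebo wounds are closed, with the same latent shift, the open-only difference is about -0.33 against -0.40 with closed coded 0, and power drops by only about 6 percentage points. A second model, with correlation 0.7 between healing propensity and colour and 60% against 77% closed, gives an open-only difference of 0.06 points in favour of JSD (power about 4%), against 0.41 (about 26%) with closed coded 0.

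**The case against.** The strongest reply is that the schedule is being read too literally. The opening sentence of section 2.12.1 heads seven items and cannot fit them all: Wexner is scored only after healing, healing time is a single duration, and the pain score is tied to dressing changes, which last 4 weeks. Section 2.8 gives recurrence as the purpose of the 8-, 12- and 16-week follow-ups. Figure 3, which may set the schedule by item, is not shown. Colour scoring after closure may also be settled on the case report form. This tempers the point but does not remove it. The text available assigns T1–T4 to the wound items without excepting colour, and it prints the complete scale twice with no value for a healed wound.

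Section 2.16 quotes mean healing rates of 33.35% and 27.33%, which might suggest that few wounds close. Those figures carry no time point, so they do not show that wounds stay open at T1–T4.

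Three stronger readings are tempting, and the document supports none of them:
- A reader might infer that healed participants are dropped from the colour analysis. The document does not say so. It is what follows if the cell is left blank, and coding the wound 1 or imputing a colour is equally unspecified.
- A reader might infer that the colour effect is always pulled towards no difference. That needs colour and closure to share a cause; under other assumptions the bias is nil or runs against JSD.
- A reader might take the gap between -0.49 and -0.22 as the bias. It is not, because the first figure adds closure as an extra level.

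**Conclusion.** The point holds in a limited form. As written, scale and schedule leave the best wound outcome without a colour value at visits where closure is to be expected. Unless a value is assigned, the comparison at T1–T4 is made among open wounds only, a post-randomisation subset that is smaller in the arm that heals better.

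The size cannot be established from the document. Under the stated assumptions the open-only difference is about -0.2 points with power of at most about 10%, against -0.3 (about 27%) and -0.5 (about 33%) when closed wounds are coded 1 or 0, and closure itself contributes to both of the latter. With very few closures the effect is small.

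The consequence is minor. Colour is one of seven wound items. Healing rate reaches 100% at closure and healing time ends there, so both credit healed participants, and the main efficacy reading does not rest on colour.

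**What to change.** Adopt one of two rules before the data are analysed by arm.

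1. Restrict the between-arm colour comparison to the weekly visits in weeks 1–4, report the number of closed wounds per arm at each visit beside it, and drop colour as a comparative outcome at T1–T4. The cost is the loss of late colour comparisons. Any early closures still need the count beside them for the result to be read properly.
2. Add a level to Table 2, 0 = closed, fully epithelialised, and assign it at every visit after closure. Compare all randomised participants with a rank test and label the result a combined closure-and-colour score, not a colour effect. The cost is a departure from the cited scale and overlap with healing rate and healing time.

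Neither needs new data, because closure is already recorded for healing time. The first keeps the item a measure of colour and is the simpler change.
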